# Technologies for the diagnosis of angle closure glaucoma (ACE): protocol of a prospective, multicentre, cross-sectional diagnostic study

**DOI:** 10.1136/bmjopen-2023-073975

**Published:** 2023-10-04

**Keywords:** ophthalmology, glaucoma, clinical trial, diagnostic imaging

## Abstract

**Introduction:**

Angle-closure is responsible for half of all glaucoma blindness globally. Patients with suspected glaucoma require assessment of the drainage angle by an experienced clinician. The goal of this study is to evaluate the diagnostic performance and cost-effectiveness of two non-contact tests, anterior segment OCT (Optical Coherence Tomography) (AS-OCT) and limbal anterior chamber depth for patients referred to hospital with suspected angle closure compared with gonioscopy by ophthalmologist.

**Methods and analysis:**

Study design: prospective, multicentre, cross-sectional diagnostic accuracy study. Inclusion criteria: adults referred from community optometry to hospital with suspected angle closure. Primary outcome: Sensitivity and specificity. Secondary outcomes: Positive/negative likelihood ratios, concordance, cost-effectiveness, proportion of patients requiring subsequent clinical assessment by ophthalmologist. Sample size: 600 individuals who have been referred with suspected angle closure from primary care (community optometry). We will have a 95% probability of detecting the true sensitivity of either test to within ±3.5% based on a sensitivity of 90%. The study would also have a 95% probability of detecting the true specificity of either test to within ±5%, assuming a specificity of 75%.

**Ethics and dissemination:**

Ethical Review Board approval was obtained. REC reference: 22/LO/0885. Our findings will be disseminated to those involved in eye care services. We will have a knowledge exchange event at the end of the study, published via the Health Technology Assessment web page and in specialist journals. The results will be presented at professional conferences and directly to patients via patient group meetings and the Glaucoma UK charity.

**Trial registration number:**

ISRCTN15115867.

Strengths and limitations of this studyProspective study design.Masked investigators interpreting tests and the reference standard.Adequate, large sample size.Evaluation of cost-effectiveness of the novel patient pathway.Imperfect, subjective reference standard.

## Introduction

Glaucoma is a chronic optic neuropathy and a leading cause of irreversible blindness.^1–4^ In the UK, more than 500 000 people have glaucoma, and 4000 new patients are registered each year with sight loss because of glaucoma. Many more people have glaucoma not severe enough to be registered, but severe enough to reduce vision and quality of life (eg, loss of their driving licence).^5^

Hospital eye services (HES) account for 8% of outpatient attendances to the National Health Service (NHS) and glaucoma accounts for 25% of outpatient activity of HES, with more than 1 million visits per year in England alone due to glaucoma.^5^

There are two types of glaucoma, according to the appearance of the drainage angle of the eye: open angle glaucoma (OAG), the most common, and angle closure glaucoma (ACG). In ACG, which is the subject of this study, the drainage angle is blocked, leading to acute or chronic elevation of intraocular pressure and damage of the optic nerve.

ACG is less common but more severe than OAG and its prevalence increases with age (Bourne, Tham). Acute angle closure is an uncommon but serious ocular emergency.^6 7^ In the early stage of the disease, angle closure can be treated with laser to reduce the risk of developing glaucoma and vision loss.^6 8^

ACG is responsible for approximately one in six glaucomas in the UK and a substantial proportion of glaucoma referrals to HES.^9 10^

A recent Cochrane review found suboptimal quality evidence regarding the diagnostic performance of non-contact tests, anterior segment OCT (AS-OCT) and limbal anterior chamber depth (LACD).^11^ Pooled data showed that LACD had high sensitivity and a possibly sufficient specificity for case finding and performed as well as AS-OCT but the authors highlighted ‘There is still a need for high-quality studies to evaluate the performance of non-contact tests for angle assessment’. Given the demands OAG presents the health service and the implications delays in diagnosis may have for patients, clearly it is important to assess the cost-effectiveness of potential improvements to the diagnostic pathway. Our study will fill this gap and determine the potential of these tests in the diagnosis of angle closure.

Our hypothesis is that the non-contact tests for diagnosing angle closure will be accurate and will facilitate a safe and efficient pathway for patients with this condition. The goal of this study is to evaluate the diagnostic performance and cost-effectiveness of two non-contact tests, AS-OCT and LACD for patients referred to hospital with suspected angle closure compared with standard practice (gonioscopy by ophthalmologist). This report describes the protocol V.1.0.

## Methods and analysis

### Study design

ACE is a prospective, cross-sectional, multicentre, diagnostic accuracy study of people referred to HES with suspected angle closure. Study setting is secondary care, HES.

Sampling and data collection will be carried out prospectively. Consecutive eligible patients will be approached to take part in the study (figure 1). Patients referred to HES with suspected angle closure will be approached and those who consent will undergo testing with the two non-contact technologies (index tests) on the same day. Patients will undergo AS-OCT (with any device available at the site) and the images of the temporal and nasal angle will be sent to a reading centre for interpretation. Interpretation of AS-OCT will use reference images and the investigator will determine if the angle is closed (ie, contact between peripheral iris and trabecular meshwork at one or both quadrants), open or indeterminate. In addition the investigator will grade the angle opening (<10 degrees, 10–20 degrees or >degrees) using reference images. The LACD will be performed and graded by a hospital optometrist (masked to the AS-OCT and to the reference standard). The investigator will use reference images to determine if the angle is closed (ie, contact between peripheral iris and cornea), open or indeterminate. The investigator will also grade the angle opening according to a 7-point scale proposed by Foster *et al*, using reference images.^12^ Patients will then receive the reference standard (gonioscopy), provided by an expert who will be masked to the evaluated tests (LACD and AS-OCT). The expert will be an ophthalmologist with glaucoma expertise and will judge if the angle is open or closed. Masked ophthalmologists, optometrists and trained photographers/imaging technicians will interpret AS-OCTs images provided by the reading centre at a different time.

**Figure 1 F1:**
[figure not shown]
ACE study participant flowchart. AS-OCT, anterior segment Optical Coherence Tomography; LACD, limbal anterior chamber depth.

Prior to the study recruitment we will meet clinicians and investigators at each study site to review and agree on the reference standard and interpretation of tests.

#### Inclusion criteria

Adults (≥18 years) referred from community optometry to HES with suspected angle closure, with or without additional comorbidity.

#### Exclusion criteria

Unable to provide informed consent; unable to undergo a slit-lamp examination.

The primary outcome is sensitivity and specificity of the non-contact tests to detect angle-closure. Reference standard is gonioscopy by an ophthalmologist with glaucoma expertise.

#### Secondary outcomes

Positive/negative likelihood ratios, concordance, cost-effectiveness, proportion of patients requiring subsequent clinical assessment by ophthalmologist, proportion of patients unable to undergo tests and of tests of inadequate quality.

#### Recruitment of study participants

Potential patients will be identified through referral letters from optometrists to HES. Potential patients with possible angle closure will be approached before they come for their routine clinical appointment, by phone or via an invitation letter.

Prior to the initiation of the study, training will be provided to the investigators on the interpretation and grading of the tests (AS-OCT, LACD, gonioscopy) via a web-based teaching module on AS-OCT images and LACD interpretation.

The optometrists performing the LACD test will be masked to gonioscopy. Optometrists, ophthalmic photographers/imaging technicians and ophthalmologists interpreting patients’ images will be masked to the reference standard.

Ophthalmologists performing the gonioscopic evaluation will also be masked to the optometrist LACD test result and to the AS-OCT test, including the findings/decisions made by the optometrists, ophthalmic photographers/imaging technicians and ophthalmologists (who will be reviewing the images at a later date). At the same visit participants will be asked to complete a health status questionnaire, European Quality of Life - five dimension - five level (EQ-5D-5L).^13^ The schedule of assessments is described in online supplemental appendix 1.

10.1136/bmjopen-2023-073975.supp1Supplementary data

#### Data collection and management

The chief investigator (CI) and the Northern Ireland Clinical Trials Unit (NICTU) will provide training to site staff on trial processes and procedures, including the completion of the case report form (CRF) and data collection. Monitoring during the trial will check the accuracy of entries on CRF’s against the source documents, the adherence to the protocol, procedures and Good Clinical Practice (GCP), as outlined in the trial monitoring plan.

Quality control is implemented by the NICTU in the form of standard operating procedures, which are defined to encompass aspects of the clinical data management process and to ensure standardisation and adherence to International Conference of Harmonisation GCP guidelines and regulatory requirements.

Data validation will be implemented and discrepancy reports will be generated following data entry to identify discrepancies such as out of range, inconsistencies or protocol deviations based on data validation checks programmed in the clinical trial database.

To ensure accurate, complete and reliable data are collected, the NICTU will provide training to site staff either through investigator meetings or site initiation visits.

All data for an individual patient will be collected by the principal investigator (PI) or designee and recorded in source documents and/or the CRF for the study. The EQ-5D-5L questionnaires will be completed by the patient. Patient identification on the CRF and questionnaires will be through their unique trial identifier, allocated at the time of recruitment.

CRFs and questionnaires are to be submitted to the NICTU as per the CRF submission schedule.

In addition to the data specified in the sections above, the following information will be obtained and recorded in the appropriate CRF:

The time the patient spent with a photographer/imaging technician to complete the AS-OCT images, the time the patient spent with the optometrist to complete the LACD test and time the patient spent with the ophthalmologist to complete the gonioscopic examination. This information will be obtained in a consecutive group of patients until saturation is reached.The time required by the optometrist, the ophthalmic photographer/imaging technician and the ophthalmologist to interpret the images and to determine whether there is angle closure or not.Scores obtained in the health-related quality of life (HRQOL) questionnaire (EQ-5D-5L) filled in by patients and collected at the study visit, which will provide utility data for different health states.Resource use data will be collected to explore the costs of delivering the standard care pathway and the new proposed triage pathway and to find the key cost drivers.

#### Trial management arrangements

The CI will have overall responsibility for the conduct of the study. The NICTU will undertake trial management including all clinical trial applications (Ethics and Research Governance), site initiation and training, monitoring and reports to ethics, Sponsor and Funder. The trial coordinator will be responsible on a day-to-day basis for overseeing and coordinating the work of the multidisciplinary trial team, and will be the main contact between the trial team and other parties involved. Before the trial starts, site training will take place to ensure that all relevant essential documents and trial supplies are in place and that site staff are fully aware of the trial protocol and procedures. The NICTU will assist and facilitate in the setting up and coordination of the trial committees.

#### Trial Management Group

A Trial Management Group (TMG) will be established and Chaired by the CI. The TMG will include representation from the NICTU and other investigators or collaborators who are involved in the study and provide trial specific expertise (eg, trial statistician, health economist). This group will have responsibility for the day-to-day operational management of the trial. Regular meetings of the TMG will be held to discuss and monitor progress. The discussions of the TMG will be formally minuted and a record kept in the Trial Master File. A TMG charter will be drawn up to detail the terms of reference of the TMG, including roles and responsibilities of the members.

#### Trial Steering Committee

The conduct of the trial will be overseen by an independent Trial Steering Committee (TSC). Throughout the study, the TSC will take responsibility for monitoring and guiding overall progress, scientific standards, operational delivery and protecting the rights and safety of patients enrolled in the study. The TSC will include an independent statistician, a health economist, at least two independent clinicians and a patient representative. The CI will attend the TSC meetings. Representatives of the Sponsor, Funder and the NICTU may attend TSC meetings as observers and at the discretion of the Chair. The TSC Charter will outline the terms of reference of the TSC including roles and responsibilities, membership, organisation of meetings (including frequency), reporting, decision-making and the relationship with the other trial committees.

#### Data Monitoring and Ethics Committee

The main role of the Data Monitoring and Ethics Committee (DMEC) will be to monitor the trial data and make recommendations to the TSC on whether there are any ethical or safety reasons why the trial should not continue. The DMEC will include a researcher, a statistician and a clinician. Attendance at DMEC meetings by non-members will be at the discretion of the Chair. The primary DMEC reporting line will be via the Chair to the TSC. The DMEC Charter will outline the terms of reference of the DMEC including roles and responsibilities, membership, organisation of meetings (including frequency), reporting, decision-making and the relationship with the other trial committees.

### Patient and public involvement

The patient and public involvement (PPI) co-applicants will be supported to convene a PPI group that will actively contribute and advise on all patient-facing and public-facing documentation, including promotional patient information leaflets, informed consent forms (ICF) and plain language summaries. They will also be involved in dissemination of the study’s results to patients and the public. The PPI group will meet during the development phase, at the end of the internal pilot phase (when the progression criteria are being considered) and at the end of the study.

#### Protocol compliance

A protocol deviation is defined as an incident which deviates from the normal expectation of a particular part of the study process. Any deviations from the protocol will be fully documented on the protocol deviation form in the CRF.

A serious breach is defined as a deviation from the study protocol or GCP which is likely to effect to a significant degree:

The safety or physical or mental integrity of the patients in the trial; orThe scientific value of the trial.

The PI or designee is responsible for ensuring that serious breaches are reported directly to the NICTU within one working day of becoming aware of the breach, using the dedicated email address ([contact]). The NICTU will notify the CI and Sponsor immediately to ensure adherence to the reporting requirements to the Research Ethics Committee (REC) where a serious breach has occurred. Protocol compliance will be monitored by the NICTU who will undertake site visits to ensure that the trial protocol is adhered to and that necessary paperwork (eg, CRFs, patient consent) is being completed appropriately.

The trial has been registered with ISCTRN (ISRCTN registry – 43107).

### Statistical considerations

#### Sample size

We will recruit 600 individuals who have been referred with suspected angle closure from primary care (community optometry). According to our feasibility work, we estimate that approximately half of these 600 individuals will have angle closure and that half will not have it. Angle closure is typically a bilateral disease, and, thus, the majority of individuals will have similar angle characteristics in both eyes but, in the rare case of an individual having angle closure in only one eye, they will be considered to have angle closure.

Previous studies have shown that using a cut-off to capture 90% sensitivity corresponds to a specificity of around 75% with AS-OCT or with LACD.^14–16^ Therefore the study will have a 95% probability of detecting the true sensitivity of either test to within ±3.5% (ie, the CI for the true sensitivity would be approximately 7% points in width), based on a sensitivity of 90%. The study would also have a 95% probability of detecting the true specificity of either test to within ±5% (ie, the CI for the true specificity would be 10% in width), assuming a true specificity of 75%. These sample sizes are conservative because they are based on using only one eye per person, while in practice, as described below, information from both eyes will be used.

#### Statistical analysis

Sensitivity and specificity will be calculated using data from both eyes, CIs will then be calculated using variance inflation factors to account for the lack of independence of each eye in the same person (using the svy function in Stata).^17^ Primary analysis will be based on a binary result, closed or not closed. A sensitivity analysis will be conducted calculating test performance measures using a multilevel logistic regression model, with eyes nested within person and person as a random effect. We will extend this model to include the site and operator of the various tests to explore the impact these have on the width of the CIs for sensitivity and specificity.

Secondary analyses will be conducted investigating different degrees of angle closure (on LACD and AS-OCT). Initially, a cut-off will be selected to obtain a sensitivity of 90% and the resulting specificity will be determined. We will explore the diagnostic accuracy of combining both tests (LACD and AS-OCT), and of using different thresholds for a positive result. We will also compare the diagnostic accuracy of AS-OCT images interpreted by optometrists, photographers/imaging technicians and ophthalmologists.

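### The secondary analysis fixes a 90% sensitivity target that three AS-OCT bands and a 7-point LACD grade cannot be guaranteed to meet, so the resulting specificity need not be specificity at 90% sensitivity

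*Protocol article*

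**What the plan says.** Under Statistical analysis, the main result uses a fixed call: "Primary analysis will be based on a binary result, closed or not closed". The article then adds graded analyses: "Secondary analyses will be conducted investigating different degrees of angle closure (on LACD and AS-OCT"). Their first step is: "Initially, a cut-off will be selected to obtain a sensitivity of 90% and the resulting specificity will be determined". The same paragraph says that other positivity thresholds, and the two tests combined, will be explored.

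Study design defines what is available to cut. For AS-OCT, "the investigator will grade the angle opening (<10 degrees, 10–20 degrees or >degrees) using reference images". The label of the third band is incomplete in the text, and nothing here depends on it. For LACD, "The investigator will also grade the angle opening according to a 7-point scale". Each test also yields a call of closed, open or indeterminate. For AS-OCT, closed means "contact between peripheral iris and trabecular meshwork at one or both quadrants". The article describes no continuous angle measurement for either test.

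The Sample size section takes 90% sensitivity with about 75% specificity as the operating point for either test, citing previous studies.

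**The concern.** A cut-off can be tuned to a chosen sensitivity when the test result is continuous or finely graded. A three-band scale offers two interior boundaries and a 7-point scale offers six. The analyst can take one of the sensitivities that those boundaries happen to give, but cannot set sensitivity to 90%.

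Two consequences follow. First, the specificity obtained belongs to whatever sensitivity the boundary has. If LACD lands at one sensitivity and AS-OCT at another, a difference in specificity partly reflects where the grade boundaries lie and not how well the tests discriminate. Second, the boundary is picked on the patients whose accuracy is then reported. The choice may differ from one study to the next, and the sensitivity shown at the chosen boundary may be biased by the picking.

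**Working it through.** **Inputs from the article.** 600 people, about half with angle closure, so about 300 and 300; operating point 90%/75%; stated precision ±3.5 and ±5 points; two AS-OCT and six LACD boundaries.

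**Assumptions.** The article gives no grade distributions and no selection rule. Several boundary layouts were therefore tried under two rules: the first boundary with observed sensitivity of *at least* 90%, and the boundary *nearest* 90%. One eye per person is used. A second, correlated eye would narrow the zone of chance somewhat but would add no boundaries.

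**1. The plan's own precision.** Half-width = 1.96 × √(p(1−p)/300).
- p = 0.90: 1.96 × √(0.09/300) = 3.4 points (stated 3.5).
- p = 0.75: 1.96 × √(0.1875/300) = 4.9 points (stated 5).

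Both reproduce.

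**2. What a miss from 90% does to specificity.** Take an equal-variance binormal ROC curve through 90%/75%: d′ = z(0.90) + z(0.75) = 1.282 + 0.674 = 1.956, and specificity = Φ(d′ − z(sensitivity)).

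| Sensitivity | Specificity |
|---|---|
| 80% | 86.7% |
| 83% | 84.2% |
| 88% | 78.3% |
| 90% | 75.0% |
| 92% | 70.9% |
| 95% | 62.2% |
| 97% | 53.0% |

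A boundary at 95% instead of 90% moves specificity by 75.0 − 62.2 = 12.8 points, against a planned half-width of 5.

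**3. How close a boundary is likely to be.** With boundaries placed at random on the probit scale between sensitivities of 30% and 99.5% (an assumption), the nearest of two lay within 3.5 points of 90% in 24% of layouts, and the nearest of six in 58%.

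**4. Chance in the choice.** The exact binomial probability (n = 300) that a boundary shows at least 90% is 16% if its true sensitivity is 88%, 33% at 89%, 55% at 90% and 91% at 92%. Simulating the choice on the curve of step 2:

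| Test | Neighbouring boundaries (true sensitivity) | *At least 90%* | *Nearest 90%* | Specificities |
|---|---|---|---|---|
| LACD | 88% / 92% | 16% / 75% (9% go to the next, at 97%) | 52% / 48% | 78% / 71% |
| LACD | 90% / 95% | 55% / 45% | 96% / 4% | 75% / 62% |
| LACD | 86% / 94% | 2% / 97% | 51% / 49% | 81% / 66% |
| LACD | 80% / 95% | 0% / 100% | 5% / 95% | 87% / 62% |
| AS-OCT | 70% / 97% | 0% / 100% | 0% / 100% | 92% / 53% |
| AS-OCT | 83% / 97% | 0% / 100% | 52% / 48% | 84% / 53% |

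Among the near-even splits, the gap in specificity runs from 78.3 − 70.9 = 7.4 points to 84.2 − 53.0 = 31.2 points. Over random 7-grade layouts, the same boundary was picked in fewer than 90% of repeat studies in 43–44% of layouts, and in at least 99% of repeats in 33–38%.

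**5. Bias from choosing and reporting on the same patients.** A boundary with true sensitivity 89% passes an *at least 90%* rule in 33% of studies. In those, the mean observed sensitivity, E[X/300 | X ≥ 270], is 91.0%, which is 2 points too high. Specificity at a given boundary is estimated from different people, those without closure, so the picking does not bias it. It misleads only if it is labelled as specificity at 90% sensitivity.

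**The case against.** A reader might infer that 90% cannot be reached on AS-OCT at all, or that the LACD choice is simply a matter of luck. The documents support neither. One of two boundaries may fall near 90%, and the indeterminate category and the two quadrants could add levels to AS-OCT. The Sample size section reports that earlier studies found a 90%/75% cut-off for both tests, although whether on these grade scales cannot be seen. Instability is conditional. With LACD boundaries at 90% and 97% sensitivity, *at least 90%* splits 55/45, but *nearest 90%* takes the 90% boundary in 99.7% of simulated trials. All of this stands. It limits the finding to a target that cannot be guaranteed and a choice that can be unstable.

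The analysis is also secondary. Specificity at 90% sensitivity is not among the listed secondary outcomes, and the plan to explore different thresholds overlaps with reporting every boundary. That lowers the stakes, but the 90% sentence stays as written. The article plans no head-to-head of the tests at this cut-off, so non-comparability is a caution for whoever reads the two figures together, not an error in a planned comparison.

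Finally, the selection rule and interval method may be in a statistical analysis plan that is not shown. Their absence is therefore not the point. The point is that two statements in the article do not fit: a numerical sensitivity target, and grades too coarse to ensure it.

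**Conclusion.** The concern holds in a limited form. On the recorded grades, 90% sensitivity is a target that may be missed, and for AS-OCT a close hit is unlikely (24% of random two-boundary layouts came within 3.5 points). The specificity that results belongs to the sensitivity actually attained and should not be presented as specificity at 90%.

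Instability ranges from almost none to about 50/50, with roughly 7 to 30 points of specificity between the competing boundaries. In about a third of the assumed 7-grade layouts the choice is practically fixed, and any fault there is a miss from 90% and not chance. These sizes rest on the assumed curve, layouts and rules; the article gives no data to narrow them.

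It would be wrong to extend this to the main result. The primary analysis uses a fixed closed/not closed call with no selected cut-off, and the stated precision reproduces.

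**What to change.** Replace the 90% cut-off sentence under Statistical analysis. Report sensitivity and specificity, with intervals clustered by person, at every grade boundary of both tests (two for AS-OCT, six for LACD), and name one boundary per test before the data are seen. If specificity at 90% sensitivity is still wanted, interpolate it on the empirical ROC curve and bootstrap persons, repeating the interpolation in each resample.

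No extra data are needed. The cost is a change of wording, a little more analysis, and a wider interval for the interpolated figure.
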